### Study aims and hypotheses

The goal of the POKAL-PSY study is to find relevant risk-factors and predictors determining the severity of unipolar depression in an outpatient setting with a data driven approach. In Addition, easily retrievable parameters should be used to facilitate the diagnostic process in an outpatient setting. To achieve this, we will use clinical parameters as well as a wide array of biological markers such as IGF-1, cortisol, AAT-1, and HRV measurements. We will recruit three cohorts consisting of outpatients with depression at inclusion, patients in primary care without psychiatric disorders, as well as healthy controls with no prior medical history. Moreover, in a cross-sectional analysis, we are aiming to determine whether we can use data-driven algorithms to identify new relevant sub-categories of unipolar depression that are not yet included in current classification systems. In a further step we would investigate the outcomes of each subcategory.

Accordingly, we assume:Functional and structural physiological correlates exist (autonomic nervous system, blood count, inflammatory parameters, fat distribution patterns) that are altered in the presence of depression compared to healthy, or somatically ill but not depressed patients.Physiological and phenotypic differences exist within the overall population of all depressed patients, which influence the outcome and further course of the disease.

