#### Secondary outcomes

Furthermore, we will implement a prospective algorithm predicting the severity of the participants' depressive symptomatology after one year. The results will be compared with the expertrating conducted at baseline. To ensure generalizability we will test the cross-sectional algorithm on the follow-up data. Further we will conduct a structural equation model (SEM) analysis at inclusion to better understand the underlying mechanisms that drive unipolar depression. Unsupervised cluster algorithms will be used to detect biomarker driven subtypes.

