### Planned data analyses

Categorical data will be one-hot-encoded if suitable and summarized with percentages and confidence intervals. For ordinal data the median will be given as well as the interquartile range and for continuous data we calculate the mean as well as the standard deviation and the confidence intervals. Demographic and baseline characteristics in the study arms will be compared with suitable statistical tests. Since multiple comparisons will be performed significant *p*.values will be reported false discovery rate corrected [107]. With the cross-sectional data at inclusion a SEM analysis will be conducted [108]. Furthermore, we will investigate the predictive value of baseline biological parameters for change in depressive symptomatology. In addition, we will design a classification algorithm using all relevant data detecting which participant is depressed. This approach involves the implementation of multiple supervised machine learning algorithms to thoroughly assess their performance. We will evaluate each algorithm during the analysis stage and subsequently select the one that yields the most favorable results. These algorithms may include, but are not limited to, support vector machines, decision trees, and neural networks. Each of these algorithms will be carefully applied and evaluated in the context of our research question. Furthermore, we will use multimodal stacked algorithms to assess the generalizability of different clinical questionnaires and biomarkers separately. To ensure the robustness of our algorithm selection and model performance assessment, we will employ a leave-site-out nested cross-validation approach in each model. This mitigates the risk of overfitting and ensures generalizability. Since the eventual goal of our algorithm is the implementation in a clinical context and to guide general practitioners, we plan to develop a sequential prediction model, which reduces the number of required data modalities and diagnostic uncertainty, as described by Koutsouleris et al. [109]. Sequential stacking models can be used to reduce the data required to produce optimum prediction scores. This method can greatly increase clinical applicability since physicians will be only asked for additional information if needed to achieve satisfactory predictive accuracy [109].

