Further, we recognize the necessity of employing cluster analysis techniques to gain insights into the heterogeneous nature of depression [17]. It is likely that depression does not encompass a single biological phenotype but rather multiple distinct profiles. To comprehensively address this, we will utilize various clustering algorithms. Our primary clustering algorithm will be non-negative matrix factorization [110]. Subsequently, we will select the clustering algorithm that best aligns with the clinical realities reflected within the identified clusters.

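### The clustering plan asks whether subtypes of depression exist, but as stated it always ends in a chosen clustering and has no result that counts as no discrete subtypes

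*Protocol article*

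**What the plan says.** Study aims and hypotheses puts the matter as a question: "we are aiming to determine whether we can use data-driven algorithms to identify new relevant sub-categories of unipolar depression". The Secondary outcomes section words it as a task: "Unsupervised cluster algorithms will be used to detect biomarker driven subtypes".

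The clustering paragraph of Planned data analyses gives the procedure. It first presumes the answer: "It is likely that depression does not encompass a single biological phenotype but rather multiple distinct profiles". It then says "we will utilize various clustering algorithms" and names the lead method: "Our primary clustering algorithm will be non-negative matrix factorization". It closes with the deciding step: "we will select the clustering algorithm that best aligns with the clinical realities reflected within the identified clusters".

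Two neighbouring statements bear on this. The aims foresee a follow-on: "In a further step we would investigate the outcomes of each subcategory". The paragraph on supervised prediction, which precedes the clustering paragraph, says "we will employ a leave-site-out nested cross-validation approach in each model".

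**The concern.** A question about whether something can be found needs a procedure that can answer no. Here the last stated step is a choice among clusterings already obtained, judged on how well they match clinical expectation. Each branch therefore delivers a set of clusters.

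NMF and k-means-type methods run with two or more clusters divide any sample, including one drawn from a single continuous population. The article itself describes links between metabolic, inflammatory and autonomic markers, and such links make the divisions look orderly.

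If the statement that subtypes exist rests on this procedure alone, it does not depend on whether they do. Later comparisons of outcome by subtype, and the suggestion under Strengths and limitations that patient groups might benefit from differing treatment approaches, could then rest on arbitrary cuts through a continuum.

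**Working it through.** **The plan's own figure.** The only calculated sample size is 870, for the structural equation model. It reproduces exactly with the usual a priori lower bound (effect 0.15, power 0.90, 5 latent variables, two-sided alpha 0.05, Sidak-adjusted over 5 × 4 / 2 = 10 latent pairs). It has no bearing on the clustering, for which no figure is stated.

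**Inputs.** From the Power calculation: 475 patients with depression. Assumed: 15 or 20 markers, their correlations, normal margins, and a marker-severity correlation of 0.15. All data sets came from one population with no subgroups.

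**Check 1: does NMF divide a homogeneous population?** Each patient goes to the component with the largest weight; markers are scaled to 0-1. With 20 markers and 60 runs per setting:

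| Marker correlation | k | Markers differing (of 20, Bonferroni) | Split-half adjusted Rand index |
|---|---|---|---|
| 0 | 2 | 8.6 | 0.05 |
| 0 | 3 | 13.2 | 0.06 |
| 0.3 within three blocks | 2 | 16.2 | 0.28 |
| 0.3 within three blocks | 3 | 20.0 | 0.42 |

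At least one marker differed in every run, and the smallest cluster averaged 26-44% of patients. A repeat with separate code gave 8.7, 12.7, 16.0 and 20.0 markers and agreement of 0.03, 0.06, 0.35 and 0.47. A further set of 30 runs per setting gave smallest clusters of 25-43%, 9 to 20 markers, and agreement rising from about 0.03 to 0.30-0.49.

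With 15 markers, correlations of 0, 0.2 and 0.5, and k = 2 to 5, NMF filled every requested cluster in 60 + 58 + 59 = 177 of 180 data sets. At k = 2 the smaller cluster held 29-34% of patients, and 56-61% of markers differed at p < 0.05.

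**Check 2: can other methods return one group?** Yes. On the same 180 data sets, a Gaussian mixture with one component allowed, chosen by BIC, returned one group in 180 of 180. At correlation 0.2, a gap-type comparison with a single-population reference of the same covariance returned one group in 40 of 40.

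**Check 3: would a clinical comparison expose empty clusters?** Not reliably. Severity was given a weak continuous link to the markers. At k = 2, clusters from homogeneous data differed in severity in this share of data sets:

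| Marker correlation | NMF | k-means |
|---|---|---|
| 0 | 5% | 8% |
| 0.2 | 5% | 77% |
| 0.5 | 7% | 73% |

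A rule that leaves NMF for whichever solution fits the clinic best can therefore move towards divisions that merely slice a continuum along severity.

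**Check 4: which statistic suits a reference test?** In strongly separated groups, a split-half rule fired in 7-80% of runs. A two-cluster within/total sum-of-squares index on the same Gaussian reference fired in 87-100%. Both fired in 5% or less with no subtypes.

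**The case against.** The strongest reply is that this is a condensed article. A fuller protocol (version 3.0) exists and is not shown; it or an analysis plan may set the number of clusters, a stability criterion and a null reference. That stands for those details, and their absence is not the point here. But the article does state the step that decides the clustering, and that step presupposes clusters.

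A reader might infer that any clustering algorithm returns clusters from any data. That is too strong: the article leaves its further algorithms open, and Check 2 shows that some can return one group.

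A reader might also infer that false detection is certain, since markers differed between clusters in every run. The documents do not support this. The article nowhere treats marker differences between clusters as proof of subtypes, and it plans to look at outcomes by subcategory. Its second hypothesis, on differences among depressed patients that influence course, could also be met by a continuum. Even so, an outcome difference does not show that discrete groups exist (Check 3), although NMF clusters showed a severity difference in only 5-7% of data sets.

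The leave-site-out cross-validation does not close the gap. It is described with the supervised models. Even if it were extended to the clustering, agreement across sites would not by itself distinguish groups from shared correlation.

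Finally, split-half values of 0.28-0.49 are far from the perfect value of 1, so a strict threshold might catch some empty solutions. No threshold is stated, and the rise from correlation alone shows why one needs a reference.

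**Conclusion.** The point holds in a limited form. The stated procedure cannot return no discrete subtypes, although the aim is an open question. The named primary method divides homogeneous data into sizeable groups that differ on the markers used to form them. Clinical fit and an unreferenced stability index do not guard against this.

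The size of the effect rests on assumed marker numbers, correlations and normal margins. The qualitative result was the same at every setting tried. How often subtypes would be wrongly claimed in practice cannot be stated, because it depends on algorithms and criteria that the article does not fix. Severity is minor to moderate: a secondary outcome is affected, and the change can be made before analysis, since recruitment is expected to run to October 2027.

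**What to change.** In the clustering paragraph of Planned data analyses, keep NMF as the primary method and add a decision rule:

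- Let one group (k = 1) be a possible answer, and list the values of k to be tried.
- Choose a separation statistic in advance, for example one minus the within/total sum-of-squares ratio, or a mixture-model comparison with one component allowed.
- Simulate reference data from a single population with the same marker covariance and margins, and run them through the identical pipeline. At each k, standardise the statistic against its reference distribution, then take the most extreme value over k in both observed and reference data.
- Claim subtypes only if the observed value exceeds the 95th percentile of the reference. Otherwise report no evidence for discrete subtypes and analyse the markers as continuous dimensions.
- Do not count differences in the clustering markers, or clinical fit, as evidence that subtypes exist. Clinical fit may still help to describe clusters that pass the rule.
- Do not use split-half agreement as the sole test statistic. With 35% of patients shifted by 1.5 or 2.5 SD on 10 markers, it fired in only 11% and 48% of 100 runs (k = 2, 19 reference sets). With uncorrelated markers those shifts are distances of √10 × 1.5 = 4.7 and √10 × 2.5 = 7.9 SD.

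The cost is a paragraph of wording and some computing time; no new data are needed. The drawback is that weakly separated subtypes may not reach the threshold, so a negative result should be reported as absence of evidence. Matching the margins and taking the extreme over k were not simulated here; check the error rate and power of the full rule before adopting it.

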#### Mediating variables

Lifestyle factors, personality traits, and personal history are considered to be mediating variables. We will consider blood pressure, medication, age, and gender as confounding factors. The breathing rate is not monitored [105].

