### Potential somatic factors and biological predictors

#### Weight gain and metabolism

Considering that primary care physicians typically focus on somatic symptoms, it is important to note that unipolar depression is associated with a range of comorbidities such as increased cardiovascular risk, adiposity, dyslipidemia, as well as high blood pressure and hyperglycemia, resulting in an increased cardiovascular risk [18]. These somatic symptoms might be the main focus of primary care physicians when diagnosing and treating patients, making it even more crucial to consider the possibility of depression and its potential impact on overall health. In fact, the presence of a metabolic syndrome, which is defined as a combination of obesity, low HDL cholesterol, high blood pressure, and elevated blood sugar levels, has been linked to unipolar depression [19]. The metabolic dysregulation in unipolar depression is associated with immunologic changes, which might only affect a clinical subgroup of patients, namely patients with higher childhood trauma scores and rather atypical features of unipolar depression [20, 21]. The link between increased body fat percentage and chronic low-level inflammation [22], childhood trauma, depression, and low physical activity is well documented [22–24]. Increased body weight is associated with decreased well-being, vitality, and quality of life [25]. Weight gain may be followed by the development of metabolic syndrome [26], which increases the risk of cardiovascular disease, autonomous dysregulation [27] and type II diabetes. Patients with unipolar depression have a higher likelihood to suffer from hypercholesterolemia and triglyceridemia compared to their non-affected peers. This association was especially present in women and in patients older than 40 [28]. A lower expression of brain-derived-neurotropic-factor (BDNF), which is associated with mood disorders like unipolar depression, could be observed in mice that were put on a hypercaloric diet [29]. Another hormone that might play an important role in the context of depression and a dysregulated metabolism is Insulin-like Growth Factor—1 (IGF-1). The expression of IGF-1 is influenced by nutrition, BMI and insulin levels, as well as age, sex, and ethnicity. While IGF-1 is mainly known for being a growth hormone that also increases testosterone production [30], evidence further suggests that IGF-1 plays an essential role in dementia, cardiovascular, and metabolic diseases [31, 32]. Elevated IGF-1 levels may increase the risk of developing depression [33, 34], but seems to also mediate the rapid antidepressant effect of ketamine [35, 36].

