## Methods and design

The POKAL-PSY study is a prospective study with three cohorts, where we recruit one cohort with healthy controls (*n* = 50), patients with depression (*n* = 475) and participants without depression (*n* = 425) where participants are monitored for five years. Notably, our emphasis on recruiting individuals with and without depressive symptoms serves to comprehensively investigate the predictors and underlying mechanisms of unipolar depression. The inclusion of patients with somatic comorbidities, who frequently seek medical care, highlights a real-world scenario. For this project, participants will be recruited in a naturalistic setting. Cardiovascular factors (heart rate variability, pulse, blood pressure), metabolic factors (blood lipids, HbA1c, body fat percentage, fasting glucose, IGF-1), as well as inflammatory markers (CRP, AAT-1) will be collected. In addition, the burden of somatic symptoms, lifestyle factors (Eating behavior, chronotype, physical activity), psychopathological characteristics (depression subtype, childhood trauma, anxiety) will be assessed by questionnaires. Depressive relapses will be assessed anamnestically if they occur during the follow-up visits. Patients will be mainly recruited in general practitioner (GP) offices, affiliated with the Bavarian Research Practice Network. Currently, we are recruiting at three different sites. By the end of the recruiting process, our goal is to have recruited from 5 to 6 different sites. We plan to recruit 90% of our study cohort within several GP offices. The inclusion and exclusion criteria are checked in consultation with the treating GPs and in direct patient contact by the study staff and the patients' written consent is obtained. In addition, participants will be recruited at the psychiatric outpatient clinic of the university clinic in Munich. In the context of the POKAL project we cooperate with other research groups and projects by providing validation datasets and support concerning participant recruitment. Specifically, we will cooperate with the MIP3 project (project nr. 21–0357, German Clinical Trials Register number: DRKS00025946). The healthy controls recruited will consist of motivated German citizens. All study personnel were trained to conduct the HRV measurements, as well as the observer ratings. Organizational project management is performed by the Studienzentrum Psychiatrie (SZP) of the LMU Munich. All participants sign a written informed consent form prior to participation. The study was approved by the local ethics committee (project nr. 22–0637, date 14.09.2022) and registered at ClinicalTrials.gov (NCT05547711) and at the German Clinical Trials Register (DRKS00030203). The study presented here is a subproject of the research network POKAL (Predictors and Clinical Outcomes in Depressive Disorders; GRK 2621), which is sponsored by the German Research Foundation (DFG) [70]. Furthermore, all the participants are kindly asked whether they give written consent to participate in the Munich Mental Health Biobank, as well [71]. The POKAL-PSY study is performed in accordance with the regulations of good clinical practice and the declaration of Helsinki [72]. The eligibility criteria can be seen in Table 1.

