#### Self-rating questionnaires

Table 2 shows which self-ratings are performed at each follow-up. To increase synergies patients are asked to fill out the Munich Mental Health Biobank Project (MMHBP) questionnaire battery as part of the POKAL-PSY study at inclusion [82].

Eating and sleeping habits will be assessed by the German version of the Three-factor-Eating-Questionnaire (FEV) [87] and the Munich Chronotype Questionnaire (MCTQ) questionnaire [88]. The simple physical activity questionnaire (SIMPAQ) will be taken to examine daily-life physical activities [89]. Also, participants will be asked about their drinking habits and whether they are smoking. Personality and anxiety traits, as well as somatic symptomatology will be measured using the Personality Inventory for DSM-5 Brief Form Plus (PID5BF + M) questionnaire [90], the Somatic Symptom Disorder-B Criteria Scale (SSD-12) [91], the Patient Health Questionnaire 15 (PHQ-15) [92], as well as the 7-item Generalized Anxiety Disorder Questionnaire (GAD-7) [93]. Personal history contains assessment of trauma with the childhood trauma questionnaire (CTQ) [94] and the Primary Care PTSD Screen for DSM-5 (PC-PTSD) [95], and family history, as well as medical history of psychiatric disorders will be gathered. The experienced loneliness is captured by the Lubben social network scale (LSNS 6) [96], as well as the UCLA 3-Item Loneliness Scale (UCLA LS-3) questionnaire [97]. Perceived Resilience and Wellbeing are measured by the WHO- 5 Well-Being Index [98] and the Brief resilience scale (BRS) [99]. Functional Outcomes are rated by performing the general assessment of functioning (GAF) [100] and participants are given the World Health Organization disability assessment schedule 2.0 (WHODAS 2.0) [101].

Table 2: Shows all planned examinations during the study period.

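### Childhood trauma is given the role of a mediator although it precedes both the inclusion biomarkers and the current depression; used that way, the secondary SEM would count confounding in its indirect and total biomarker effects

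*Protocol article*

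**What the plan says.** The section *Mediating variables* assigns causal roles in two sentences: "Lifestyle factors, personality traits, and personal history are considered to be mediating variables", and "We will consider blood pressure, medication, age, and gender as confounding factors".

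The section *Self-rating questionnaires* says what the first group holds: "Personal history contains assessment of trauma with the childhood trauma questionnaire". The same sentence adds a PTSD screen for primary care. It then says, in a separate clause, that family history and psychiatric history are collected.

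The background section *Weight gain and metabolism* says of the immunologic changes that accompany metabolic dysregulation in depression: "which might only affect a clinical subgroup of patients, namely patients with higher childhood trauma scores". It then describes as established a link that joins body fat and low-level inflammation with "childhood trauma, depression, and low physical activity is well documented".

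Blood pressure, a confounder in *Mediating variables*, also stands in *Methods and design* among the biological factors to be collected: "Cardiovascular factors (heart rate variability, pulse, blood pressure".

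The SEM is a secondary outcome, run on the inclusion data and meant to explain mechanisms (*Secondary outcomes*, *Planned data analyses*). The discussion values SEM because it can test indirect as well as direct relations. The sample size of 870 was derived for this SEM (*Power calculation*).

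**The concern.** A mediator must come after its exposure and before its outcome. Childhood trauma in adults aged 18 to 70 lies before both a biomarker measured at inclusion and the depression rated on the same occasion. The path biomarker → trauma → depression is impossible in time, and so is depression → trauma → biomarker. An early exposure that the article itself links to the metabolic and inflammatory side and to depression is a candidate common cause. The confounder list nevertheless names only blood pressure, medication, age and gender.

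At stake is the mechanistic reading of the SEM. With trauma placed between biomarker and depression, the product of two confounding paths would appear as an indirect effect of the biomarker and be added to its total effect. Model fit would give no warning, because the two orderings reproduce the same covariances.

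**Working it through.** **The plan's own figure.** Inputs from *Power calculation*: effect size 0.15, power 0.90, alpha 0.05, 5 latent variables. The standard a-priori lower-bound formula for an SEM, taking the 10 pairs of latent variables and a two-sided Šidák-adjusted alpha of 1 − 0.95^(1/10), gives 869.2, rounded up to 870. The target of 950 follows from a loss of 1 − 870/950 = 8.4%, in line with the stated allowance of slightly under 10%. The sample size is not at fault, and relabelling variables does not change it.

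**Spurious indirect effect.** Let trauma M cause the biomarker X (standardised path a) and depression Y (path b), with no effect of X on Y. Now fit X → M → Y with a direct path X → Y:

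- The X → M slope is a, and the M → Y slope given X is b.
- The reported indirect effect is a·b, although the true biomarker effect is zero.
- The direct X → Y coefficient is 0.
- Sobel SE = √(a²·se_b² + b²·se_a²), with se_a² = (1 − a²)/n and se_b² = (1 − b²)/[n(1 − a²)].

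The values of a and b are assumptions; the article gives none. At n = 870:

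| a | b | se_a | se_b | a·b | Sobel SE | z |
|---|---|---|---|---|---|---|
| 0.15 | 0.20 | 0.0335 | 0.0336 | 0.030 | 0.0084 | 3.58 |
| 0.25 | 0.30 | 0.0328 | 0.0334 | 0.075 | 0.0129 | 5.81 |

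**Simulation check** (4,000 data sets per setting, n = 870, data generated with trauma as common cause, fitted with trauma as mediator, joint test at 5%):

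| a | b | true biomarker effect | indirect | direct | total | indirect effect significant |
|---|---|---|---|---|---|---|
| 0.15 | 0.15 | 0 | 0.022 | 0.00 | 0.022 | 98.5% |
| 0.20 | 0.30 | 0 | 0.060 | 0.00 | 0.060 | 99.98% |
| 0.30 | 0.40 | 0.15 | 0.120 | 0.149 | 0.27 | 100% |

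The last row uses paths above the assumed range. It shows the pattern when a real effect exists: the direct coefficient recovers 0.15, while the total is inflated to 0.15 + 0.30 × 0.40 = 0.27.

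**Blood pressure, a separate matter** (illustrative paths):

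- If it lies on the pathway (biomarker → blood pressure 0.3, blood pressure → depression 0.3, direct effect 0.15), the total effect is 0.15 + 0.09 = 0.24. Adjustment leaves 0.15.
- If it is a common effect of biomarker and depression (0.3 each) and the biomarker has no effect, adjustment gives (0 − 0.3 × 0.3)/(1 − 0.3²) ≈ −0.10, a false negative association.

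Neither case produces a false indirect effect.

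**The case against.** The strongest reply is that the article names no exposure, no outcome and no path diagram. *Mediating variables* does not mention the SEM, and the full protocol may hold the path model. This stands in part: it cannot be said that the trial will report spurious mediation, only that it would if the stated role is used. It does not rescue the label, because no ordering of an inclusion biomarker and current depression puts childhood trauma between them.

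Several stronger readings are tempting and are not supported:

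- **That the biomarker paths are left unadjusted for trauma.** With a direct path in the model, that path is estimated conditional on the mediator, as the simulation shows. Only the indirect and total effects are distorted.
- **That all personal history precedes the biomarkers.** The PTSD screen may capture adult events, and family history is named in a separate clause. The timing argument is firm for childhood trauma and natural for family history. For personality traits it is likely but less clear-cut.
- **That trauma is proven to be a common cause.** The background reports associations and a subgroup, which would also fit effect modification. It is a candidate, and that is enough to rule out ignoring it.
- **That the lifestyle label is wrong.** Eating behaviour, chronotype and activity could be mediators, confounders or consequences of depression. The article's discussion concedes that cross-sectional data cannot separate cause from consequence. The label is unsupported, not refuted.
- **That treating blood pressure as a confounder creates false mediation.** It cannot. Its listing may even be meant as a covariate for heart rate variability.

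The size is also illustrative. A product of two paths is not the same kind of quantity as the planning effect of 0.15, so 0.075 should not be read as half of it.

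**Conclusion.** The role given to childhood trauma is wrong as written and should be corrected before the SEM is fitted. If it is used as stated, the spurious indirect biomarker effect is about 0.03 to 0.075 and would almost always be significant at n = 870. This rests on assumed correlations of 0.15 to 0.25 (trauma-biomarker) and 0.20 to 0.30 (trauma-depression), a linear model, and trauma acting as a common cause with no true biomarker effect. With a true effect, the same product is added to the total.

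The damage is confined to indirect and total effects in a secondary analysis. A reader might infer that the primary outcome or the sample size is compromised. Neither is: the prediction algorithm does not depend on these labels, and 870 and 950 reproduce from the plan's inputs. The two listings of blood pressure are a lesser, separate inconsistency, with a risk of over-adjustment or collider bias.

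**What to change.** Before analysis:

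1. State the exposure, mediator and outcome for each SEM path.
2. Enter childhood trauma and family history as exogenous antecedents with paths to both biomarkers and depression. Do the same for personality traits unless a mediating order is justified. Report no indirect effects through them.
3. Label lifestyle mediation exploratory, and add a sensitivity model with the alternative ordering.
4. Reconcile the role of blood pressure between *Methods and design* and *Mediating variables*, and show the SEM with and without adjustment for it.

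The cost is re-specification of one secondary model. All variables are already collected and the sample size stays as it is. The reported indirect and total biomarker effects may become smaller.
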